## Methods

### HMZ 2.0 Intervention Description

HMZ 2.0 is a multidosage, individually-tailored, adaptive intervention with social cognitive theory and behavior components [15-17]. The “baseline dosage” is delivered to all intervention participants, and it consists of up to 24 weekly modules (depending on gestational age at study enrollment) including the following:

Education: Knowledge-based content on meeting guidelines (GWG, PA, EI, sleep behaviors, and good sleep hygiene) [1,2,69-75]; mood (eg, depressive symptoms, stress, and anxiety); safely engaging in prenatal exercise; and awareness of stressful situations that prompt uncontrolled and emotional eating, hunger cues, cravings, and mindful eating choices [76,77]. We also provide knowledge about recently published evidence-based studies on how a mother’s health impacts her baby (eg, sleep, brain development, and food preferences) and developmental milestones (eg, when eyebrows develop), which is shared over the course of the intervention. Our pilot work [42] demonstrated that women specifically asked for education materials that provided this information.Personalized behavior coaching or counseling: Individually tailored behavior coaching from a prenatal fitness instructor and registered dietitian on GWG, PA, and EI that uses information and feedback from a woman’s prior week to inform the future week’s motivational cues and strategies to increase PA, improve diet quality, and overcome barriers (this can be delivered in person or through a remote synchronous or asynchronous approach for future scalability).Goal setting and action planning: Guided and self-selected PA and EI goals [69-71,78] using implementation intentions to target when, where, and how each woman will work toward goals and how these PA or EI goals relate to GWG. Example goals include targets for daily steps (eg, 10,000 steps) and activity time (eg, 30 minutes), as well as fruit or vegetable intake for lower energy density [79] and increasing water intake to maintain good hydration [80,81]. HMZ trimester-specific prenatal PA and recipe booklets (developed by our team) provide detailed examples for PA (eg, 150 min/week of moderate-intensity activities; 10,000 steps/day) and EI kcal goals [78].Self-monitoring: Women use mHealth tools (eg, Wi-Fi weight scale, activity monitor, and dietary intake app) to self-monitor GWG, PA, or EI [82]. The HMZ digital platform visually displays their daily or weekly data. Feedback is given to each woman on how to use the devices and self-monitor their behaviors in relation to their GWG and PA or EI goals [19,43,78,83].

#### Adaptive Intervention Dosage Changes

The model-based predictive control algorithm in the HMZ 2.0 digital platform continually and automatically evaluates GWG. It relies on a dynamic model and solving a receding horizon online optimization problem that identifies when a woman’s forecasted GWG is anticipated to exceed the GWG guidelines [1,2,84-86], and based on a structured sequence of decisions that form part of the model, a dosage change is recommended (Figure 4). Only women who have a forecasted need for added support to regulate GWG will receive adaptive dosages in addition to the baseline intervention. Dosages are additive such that a woman receives more intensive support for eating healthy and engaging in PA with each adaptation up to a maximum of 5 adaptive dosages. The web-based user interface provides an easy and intuitive way to integrate expert-supervised dosage change recommendations to regulate GWG. The HMZ 2.0 prenatal fitness instructor and registered dietitian review the participant’s data and recommend individually tailored behavioral strategies that are delivered through the HMZ 2.0 digital platform. Each woman’s unique preferences and past successes with PA or EI strategies are considered when customizing the dosage adaptation to promote engagement, enjoyment, and compliance, which can in turn influence GWG. These active learning strategies include, for example, multiple PA-guided workouts with a variety of prenatal cardiovascular and resistance training exercises (preapproved for safety and with physician consent for participation) [69,70], as well as healthy eating cooking demonstrations, portion size control strategies to substitute high energy density foods with low energy density options such as water-rich fruits or vegetables [43,71], using food scales and portion size containers, customized grocery planning, and meal replacements. There are a host of easy-to-adopt and practical recommendations for integrating PA or EI strategies into daily life (eg, walking in 5- to 10-minute increments throughout the day to increase PA kcal by 200 kcal/day, reduce sitting by 5 min/hour from 9 AM to 5 PM, and replace 8 ounces of whole milk with skim milk to reduce EI kcal by 100 kcal/day) to facilitate behavior change while adhering to safety standards [69,70]. All dosages can be delivered in person or through a remote approach (synchronous and asynchronous for selected sessions), depending on the participant’s preference.

**Figure 4 figure4:**
[figure not shown]
Healthy Mom Zone (HMZ) 2.0 adaptive intervention design. Participant weight is measured daily and continuously evaluated against the Institutes of Medicine (IOM) gestational weight gain (GWG) ranges. All intervention women will receive the baseline intervention plus step-up 1 plus step-up 2 during the system identification open-loop experiment. Dosages 3 to 5 are delivered to selected intervention participants based on hybrid model predictive controller (HMPC) decisions in the closed-loop experiment. HE: healthy eating; PA: physical activity.

#### HMZ 2.0 Automated Data Pipeline and Digital Platform

The data pipeline for HMZ 2.0, illustrated in Figure 5, is orchestrated by Apache Airflow [87], a workflow management platform, where daily jobs are scheduled, including (1) retrieving deidentified data from various sources, such as the application programming interface (API) of the REDCap [88] database; (2) preprocessing survey data, including aggregating subscales and back-calculating EI [89,90]; (3) imputing missing data via multiple imputation [91,92] and machine learning–facilitated [93-95] techniques programmed into the platform; (4) feeding the imputed data into the advanced hybrid model predictive control system to generate the adaptive decision-making process; and (5) continuously monitoring errors and warnings in the Airflow monitoring dashboard during steps 1-4, scanning data quality, and initiating automated alerts that notify different pillars of the study team based on the issue type. As the participants in the study cohort change with time, tasks for each new participant are dynamically created. The scripts are version controlled, and data generated throughout the pipeline are saved in a PostgreSQL relational database to ensure data reproducibility. The HMZ 2.0 web-based platform has been built with Django, an advanced Python web framework to scale-up future production and access (see Figure 6 for the digital platform architecture and website examples). Heterogeneous user interfaces have been built for study staff (and future clinicians), participants in the intervention group, and participants in the control group. The web-based platform provides an access-controlled admin dashboard where authorized users can manually update settings, curate data, or export deidentified datasets for further analyses. For example, during intervention sessions, study staff can access participants’ general information, data, educational content, goals, and intervention dosages, and participants will have access to selected resources that are tailored to their specific needs.

**Figure 5 figure5:**
[figure not shown]
Healthy Mom Zone (HMZ) 2.0 data transfer pipeline. API: application programming interface; GWG: gestational weight gain; HMPC: hybrid model predictive controller. *Real-time deidentified 24-hour data stream into REDCap, **Access control (user ID) by authorized study staff, ***Access control (user ID) by intervention study staff (and in the future, dissemination to clinicians).

### Recruitment

Recruitment began in April 2024 and will continue through May 2027. Pregnant women with overweight or obesity (N=144) are being recruited for this study. Our team has extensive expertise with recruiting pregnant women. Our past studies have yielded over 3100 subject contacts, with recruitment rates of 84%-92% across our studies [19,96-102]. Well-established methods from our past studies are used for recruitment procedures as follows:

Clinic: Nurses identify eligible women at the 1st prenatal visit (eg, appointment schedule and electronic health record) and refer them to the study team for screening. A study flyer with study contact information and a QR code is included in the clinic’s prenatal packet and posted in exam rooms.Community: Study flyers are posted in local areas (eg, daycares and churches) and hospitals, and shared at community events (eg, farmer’s markets and celebratory events).Social media: Study information is shared on Facebook, Instagram, X, YouTube, and study websites.

Using well-established procedures from our past studies [19,96-102], interested participants, regardless of recruitment method, are screened for eligibility. If interested, participants scan a QR code that directs them to a REDCap survey to complete a screening questionnaire or they send a message by email, text, or voicemail, and a trained study staff member will reply to complete the screening questionnaire over the phone.

The staff member reviews the participant’s responses to determine eligibility. The inclusion criteria are as follows: age range 18-45 years; singleton pregnancy with ≥8 and <18 weeks gestation; any parity; any race or ethnicity; BMI of 24-45 kg/m^2^ (>40 with provider consent); have not gained >25% of total GWG (based on BMI and IOM guidelines) from prepregnancy to the date of enrollment [103]; able to read or understand English; access to a computer or phone; able to attend sessions either on-site or remotely; randomization to conditions; no absolute contraindications to PA (and presence of relative contraindications only with health care provider consent to participate); and not a current heavy smoker (>20 cigarettes per day) [19,69-71] . The exclusion criteria are as follows: outside the age, BMI, gestation, or GWG range; not able to participate (cannot read or understand English, no access to a phone or computer to attend sessions remotely, and cannot use a device or service assistance); absolute contraindications to PA [69-71] or relative contraindications to PA noted by the participant’s health care provider as precluding study participation; current heavy smoker (>20 cigarettes per day) at study entry; and multiple pregnancy. Eligible women are scheduled for the preintervention assessment. Women not meeting the eligibility criteria are thanked for their time and given information on other studies that may be of interest.

### Safety Considerations

Prior to enrollment, a study team member informs the participant’s health care provider about their potential participation and obtains consent from each provider. The provider completes the consent form (hard copy or REDCap link) confirming eligibility for participation, and the participant is officially enrolled. This process is repeated at mid-study (eg, between the 2nd and 3rd trimesters) to ensure the participant does not have any new medical conditions that may impact study participation.

Because this study includes pregnant women, a vulnerable population as defined by the National Institutes of Health, there is a Data Safety and Monitoring Board with experts in obstetrics and gynecology, prenatal weight gain, PA and nutrition interventions, and fetal growth that will: (1) review the study methodology and procedures, data on recruitment, enrollment and adherence to the inclusion/exclusion criteria, and participant’s progress through the study; (2) assure the safety of the study participants; and (3) make recommendations to the research team. Adverse events that the Data Safety and Monitoring Board will be notified of and oversee include: (1) insufficient GWG: indicators of insufficient GWG are weight loss of less than 3% in a week or 0% weight gain in a 4-week cycle [104]; (2) depressive symptomology: all women regardless of initial preintervention assessment scores will be given resources on managing depressive symptoms and a comprehensive list of available resources and supportive services, and depressive symptoms will be monitored monthly [105]; and (3) absolute or relative contraindications to exercise [69-71].

Participants in the intervention group complete verbal assessments of pregnancy symptoms (eg, mild muscle cramping, headaches, and symptoms of labor) and contraindications to exercise (eg, bleeding, severe abdominal cramping, nausea, etc) during activity sessions. The study safety protocol includes steps to understand symptoms, ratings of perceived exertion, and responses if appropriate, including stopping the activity, seeking medical attention, and calling a participant’s emergency contact and provider. If a woman experiences a contraindication to PA in pregnancy that precludes her continued participation, she will remain in the study and complete measures as appropriate (intent to treat) but will not engage in PA until provider consent to return to activity is obtained. We also monitor changes in health status and health symptoms. For example, women who develop gestational diabetes during the study will remain in the study and receive the standard of prenatal care by their obstetrician or health care provider, in which an established standard of care plan is provided for the treatment and management of gestational diabetes.

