### Primary Outcome

#### Participant GWG

Weight and GWG are assessed daily at preintervention, during the intervention, and at postintervention at home using the Fitbit Aria Wi-Fi Smart Scale [112] (weights are wirelessly uploaded to an online program). GWG is standardized, and the target weight gain is determined for each woman based on the BMI status (overweight, 14.1-22.7 kg; obese, 11.3-19.1 kg) [1,2]. For the criterion measure to determine when to adapt the intervention, weight gain is calculated to determine if a woman is gaining less than her goal, at the exact amount of her goal, or more than her goal. GWG over the course of the study is calculated as the last measured weight during the study subtracted by the first measured weight during the study. Weight at enrollment is measured, and prepregnancy weight and GWG from the first prenatal visit to the last predelivery weight are abstracted from clinical records.

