##### EI Behavior: Back-Calculation Estimation

EI is estimated daily at preintervention, during the intervention, and at postintervention from measured weight (Aria Wi-Fi scale) [112], PA (Fitbit Charge 6 activity monitor) [112], and resting metabolic rate (RMR), with k=1, 2,… N relating to day 1 to day N. T is the sampling time (T=1 day) [8,12,68-71], and RMR is estimated daily as follows:

eRMR = 0.1976W^2^ – 13.424W + 1457.6 **(1)**

The noise in weight is small relative to the total weight, but the extent of this noise can affect the calculated rate of GWG per day, so a 5-day moving average filter is used to preprocess (smooth) measured weight before “true” daily EI is estimated [117-119]:

Our team effectively used this back-calculation method for estimating EI in the HMZ proof-of-concept study [42] and feasibility-initial impact randomized trial [8,10,19,43-45].

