### Power Calculations

The primary outcome is GWG: absolute difference between the intervention and control groups for the mean change in GWG from the start to the end of the trial. From our feasibility study [19], we found that the difference between the intervention and control groups with respect to the absolute mean change in GWG from the start to the end of the trial was 1.9 kg (SD 4.9 kg), with an approximately 21% relative reduction for the intervention group compared to the control group. We compared the mean change in our feasibility trial [19] to that in several other GWG studies comparing intervention and control groups [29,151-154] and found that the intervention group gained on average 1.8 kg less than controls (range: 1.1-3.1 kg). The sample size of 144 randomized to the intervention (n=72) and control (n=72) groups in the proposed research is informed by our feasibility trial showing a mean difference of 1.9 kg (SD 4.9 kg), a 21% relative reduction in GWG in the intervention group compared to the control group, and a 3% dropout. Given our experience with the feasibility trial [19], the series of refinements that we performed following the feasibility trial (eg, adding content on sleep and eating behaviors given their effects on GWG; modifying all content for remote delivery given 100% compliance found for remote sessions in the feasibility trial; replacing the initial control system to make dosage change decisions with the new, automated, dynamic model-based predictive control system that outperformed the initial system for regulating GWG; and adding the novel HMZ 2.0 digital platform to adapt dosages), and the findings from our HMZ 2.0 pilot study (average weekly GWG over the 4-week study period: 0.3 kg, SD 0.4 kg; overall GWG from pre- to postintervention: 1.2 kg, SD 0.8 kg), we expect the HMZ 2.0 intervention to be more effective. We anticipate that our mean difference will be closer to what a recent study [155] found for the mean difference in GWG between the intervention and control groups (mean 3.6 kg, SD 5.7 kg). Conservatively, considering this larger SD of 5.7 kg and anticipating a larger dropout rate of 10%, the sample size of 144 yields 80% statistical power with a 2-sided significance level of .05 to detect an absolute difference of at least 2.9 kg in GWG between groups. Sample sizes for semistructured interviews are adequate to observe data saturation [136,137,141].

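### The weekly safety indicator for insufficient gestational weight gain points the wrong way: small losses meet it, and losses of 3% or more do not

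*Protocol article*

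**What the plan says.** The protocol article, Safety Considerations, describes the board's remit: "Adverse events that the Data Safety and Monitoring Board will be notified of and oversee include: (1) insufficient GWG". It then gives the criterion: "indicators of insufficient GWG are weight loss of less than 3% in a week or 0% weight gain in a 4-week cycle". These are the only numerical indicators of insufficient gain in the article. No other section restates them, reverses the direction or adds a separate rule for a weekly loss of 3% or more.

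The data behind the indicator are described under Participant GWG: "Weight and GWG are assessed daily at preintervention, during the intervention, and at postintervention at home using the Fitbit Aria Wi-Fi Smart Scale". Both arms follow the same measurement schedule (Attention Control Condition). Safety Considerations also mentions a study safety protocol, which the article does not reproduce.

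**The concern.** An indicator of insufficient gain should be met when loss is large. This one is met when loss is small and stops being met once loss reaches 3%. If any weekly loss were meant to count, the 3% figure would serve only to exempt the largest losses, which cannot be the intention.

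The trial tests an intervention that restrains weight gain in pregnancy, so excessive loss is a foreseeable harm, and this sentence sets when the board hears of it. Applied as written, it could fail in two ways:

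- **Too many notifications.** Ordinary week-to-week variation would meet the indicator often, and a notification that common carries little information.
- **Missed losses.** A loss of 3% or more would not meet the weekly indicator. It would reach the board under the stated indicators only through the 4-week one, if at all.

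**Working it through.** The article gives no figure to reproduce here, so the check is of direction first and of size second.

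**1. Direction.** Compare the rule as worded (loss above 0% and below 3%) with a correctly directed rule (loss of 3% or more):

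| Weekly loss | As worded | 3% or more |
|---|---|---|
| 0.1%, 0.5%, 1%, 2%, 2.9% | met | not met |
| 3%, 3.5%, 5% | not met | met |

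The two rules disagree at every value.

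**2. What 3% means in kilograms.** Recruitment admits "BMI of 24-45 kg/m^2^ (>40 with provider consent"). Height is not given. For assumed heights of 1.55-1.75 m, weight runs from 24 × 1.55² = 57.7 kg to 45 × 1.75² = 137.8 kg, so 3% is about 1.7 to 4.1 kg. For an assumed woman of BMI 32 and 1.63 m, weight is 32 × 1.63² = 85.0 kg and 3% is 2.55 kg.

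**3. How often ordinary variation meets the rule as worded.** Power Calculations reports for the pilot: "average weekly GWG over the 4-week study period: 0.3 kg, SD 0.4 kg". It also gives an overall pilot gain of 1.2 kg, SD 0.8 kg. Since 4 × 0.3 = 1.2 and 0.4 × √4 = 0.8, the 0.4 kg behaves like a week-to-week SD with independent weeks. Assuming normal weekly changes at 85 kg:

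- P(−2.55 < change < 0) = Φ((0 − 0.3)/0.4) − Φ((−2.55 − 0.3)/0.4) = Φ(−0.75) − Φ(−7.1) = 0.227.
- Low end of the range: mean 0.32 kg/week (highest target rate in Control Optimization Trial Procedures), assumed SD 0.3 kg, gives 0.143.
- High end: mean 0.18 kg/week (lowest target rate), assumed SD 0.5 kg, gives 0.359.
- At least one such week in 4, weeks independent: 1 − (1 − 0.227)⁴ = 0.64.
- Expected number over 24 weeks (the maximum number of weekly modules): 24 × 0.227 = 5.4.
- P(loss of 3% or more) with mean 0.3 and SD 0.4: below 10⁻⁷ at both 63.8 kg (BMI 24, 1.63 m) and 85 kg.

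**4. The missed side.** Suppose the 85 kg woman loses 3 kg evenly over 7 days, 0.43 kg per day:

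| Day | Cumulative loss | Percent | As worded |
|---|---|---|---|
| 1 | 0.43 kg | 0.5% | met |
| 5 | 2.14 kg | 2.5% | met |
| 6 | 2.57 kg | 3.03% | not met |
| 7 | 3.00 kg | 3.5% | not met |

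A rolling daily check would register the loss early and then stop registering it as it worsened. A single check on day 7, or an abrupt drop, would not register it at all.

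**5. Whether the 4-week indicator covers the gap.** Read as no net gain, it catches a loss that persists, but only over the 4-week cycle, and not one that is regained within it. Read literally as 0% gain, it does not name a net loss.

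**The case against.** The strongest reply is that this is a one-word slip whose intent is easy to recover: an abrupt loss of at least 3%, or four weeks without gain. The percentages are called indicators of a named event, and a board with obstetric and weight-gain experts is unlikely to regard a 4% weekly loss as acceptable. The board also reviews participants' progress, gain is evaluated weekly in the intervention arm, and all women receive routine prenatal care. The safety protocol in use may have the right direction. All of this stands, and it is why harm or delay cannot be claimed as shown. It does not make the published threshold right.

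The frequency figures are also open to challenge. They come from 10 women over 4 weeks, extended under assumed normality and independence, and they matter only if staff apply the literal rule. The range uses target rates, and women who gain faster, as controls are expected to, would meet the rule less often. EI Behavior: Back-Calculation Estimation does warn that scale noise can distort the daily rate of gain, but it calls the noise small relative to total weight, and it concerns energy intake rather than safety monitoring. So 23% indicates an order of magnitude, and the 4-week and 24-week figures are illustrations. The direction error depends on none of them.

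Finally, the article does not support assuming a single fixed weekly check. That limits the missed side to abrupt losses or once-weekly checks.

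**Conclusion.** The concern holds. The weekly indicator is reversed as written, and nothing else in the article corrects it. This is a specific safety threshold stated wrongly, not a detail left to a fuller document.

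On the pilot figures, ordinary variation would meet the literal rule in roughly a quarter of woman-weeks (0.227; range 0.143-0.359), assuming normal weekly changes. A correctly directed 3% rule would be met by almost none of that variation. A loss of 3% or more falls outside the weekly indicator. Whether this delays notification depends on how the check is run and on the unseen safety protocol. The sentence should be corrected because it governs participant safety. The primary outcome, the power calculation and the analysis are not affected.

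**What to change.** - Reword the weekly indicator as a loss of 3% or more in a week, or more than 3%. The article's cited source for the criterion and the board should settle which bound applies; that source was not available here.
- Reword the second indicator as no net gain, or a net loss, over 4 weeks, so that a sustained loss is named.
- Check that the safety protocol in use carries the corrected direction. Only if it does not, re-screen the stored daily weights of women already enrolled, in both arms.

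The cost is one corrected sentence and one document check. A re-screen, if needed, would use data already collected. The Results section reports 12 of the planned 144 women enrolled, with recruitment continuing to May 2027. A correction at that stage would cover nearly the whole cohort.

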#### Attention Control Condition

Consistent with guidelines for comparator groups [106], all women in the study receive prenatal care offered by recruitment sites with routine provider visits, counseling about prenatal behaviors (eg, no smoking), and clinical oversight of health. To match attention to the intervention group, women in the control group receive (for the first 4 weeks of the study) one-on-one weekly education sessions delivered by trained study staff, and thereafter, they receive monthly education content delivered as asynchronous videos and get check-in support from study staff (eg, phone, text, and email) for the remainder of the study. Content includes topics, such as preparing for labor or delivery; benefits of behavioral pain management strategies (eg, mindfulness-based relaxation, imagery, music, massage, and deep breathing) to regulate pain after childbirth with nonpharmacological approaches [107]; and baby or child safety, health and development, behaviors, and nutrition. Content is drawn from evidence-based guidelines and materials designed by members of the study team for a patient-provider toolbox to reduce opioid pain management use after childbirth [107], as well as The American Academy of Pediatrics, The March of Dimes, The Centers for Disease Control, and The American College of Obstetrics and Gynecology [108-111]. The matched control group education content is also provided to the intervention group as supplemental material.

Both the intervention and control groups receive the same measurement protocol and frequency of measurement to understand and compare the impact of the intervention on primary and secondary study outcomes. Data are collected from each participant daily (GWG: Aria Wi-Fi scale [112]; PA, sedentary behavior, or sleep: Fitbit Charge 6 monitor [112], logs for device wear time, and PROMIS Sleep Disturbance [113,114] assessment; and self-reported hydration behaviors); weekly (self-reported online in REDCap; social cognitive determinants and EI diet quality: MyFitnessPal app on 2 weekdays and 2 weekend days) [19,115]; and monthly (self-reported online in REDCap; eating behaviors [19,116,117], psychosocial measures, cognition, pain, and temperament measures).

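### Contraindications to exercise are a DSMB event for all women, but the only repeated active check described is in intervention activity sessions, so raw counts by arm would not be comparable.

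*Protocol article*

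**What the plan says.** Safety Considerations gives the DSMB three kinds of adverse event to oversee: insufficient weight gain, depressive symptomatology, and "absolute or relative contraindications to exercise". None is restricted to one arm.

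For the third kind, the same section describes one active check: "Participants in the intervention group complete verbal assessments of pregnancy symptoms", and also of "contraindications to exercise (eg, bleeding, severe abdominal cramping, nausea, etc) during activity sessions". It goes on to describe how staff respond when symptoms arise.

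Two other routes in that section are not tied to an arm. The provider's consent is renewed once: "This process is repeated at mid-study (eg, between the 2nd and 3rd trimesters) to ensure the participant does not have any new medical conditions". There is also a general statement: "We also monitor changes in health status and health symptoms", with no instrument or frequency.

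Attention Control Condition states: "Both the intervention and control groups receive the same measurement protocol and frequency of measurement". Adaptive Intervention Dosage Changes, which includes guided workouts among its strategies, says: "All dosages can be delivered in person or through a remote approach (synchronous and asynchronous for selected sessions". It does not say which sessions are selected.

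**The concern.** The intervention asks pregnant women to do more physical activity, so contraindications to exercise are the DSMB event most closely tied to its possible harm. If women in one arm are questioned at every activity session and women in the other are not, the counts partly reflect how often someone asked.

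An excess in the intervention arm could then be a real effect or better detection, and the DSMB could not tell which from the counts. A true signal might be explained away, or a spurious one acted on.

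**Working it through.** The article gives no figure for this event, so there is nothing to reproduce. The check is to set the sections side by side and then illustrate the consequence under stated assumptions.

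**Step 1. How each DSMB event is ascertained**

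| DSMB event | Source | Same in both arms? |
|---|---|---|
| Insufficient weight gain | Daily home scale (Table 1; Attention Control Condition) | Yes |
| Depressive symptoms | Monthly monitoring of all women (Safety Considerations); monthly scale (Table 1) | Yes |
| Contraindications to exercise | Verbal check in activity sessions (Safety Considerations) | No, intervention only |

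The first two events have a common instrument and schedule. The third does not.

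**Step 2. Whether the common measurement protocol fills the gap**

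Table 1 lists no pregnancy-symptom or contraindication form. Its row on depressive symptoms and health monitoring holds only a depression scale, and its blood pressure screen is preintervention only. The daily, weekly and monthly list under Attention Control Condition includes a monthly pain measure, which is not described and is absent from Table 1. Nothing indicates that it would pick up bleeding, for example.

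**Step 3. Other routes**

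- Provider re-consent: both arms, once, at mid-study.
- General monitoring of health status and symptoms: not limited to an arm, method and frequency not given.
- Staff contact: controls have weekly one-on-one sessions for 4 weeks, then monthly videos with check-ins. Intervention women have up to 24 weekly modules. Symptom questions are not mentioned for the control contacts.
- Record abstraction: both arms, but Table 1 times pregnancy complications at delivery, which is late for ongoing oversight.

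These routes narrow the difference between arms. None is described as repeated, active questioning about contraindications.

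**Step 4. Illustration**

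Inputs: n = 72 per arm (Randomization Procedures). Assumed: the same true rate p in both arms, 10% (range 5% to 20%). Also assumed: the sparser routes find a share s of what the session checks find, with s = 75%, 50% or 25%.

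Recorded in the intervention arm = n × p. Recorded in controls = n × p × s. Apparent ratio = 1/s.

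| p | Intervention | Controls, s = 75% | s = 50% | s = 25% |
|---|---|---|---|---|
| 5% | 72 × 0.05 = 3.6 | 2.7 | 1.8 | 0.9 |
| 10% | 72 × 0.10 = 7.2 | 5.4 | 3.6 | 1.8 |
| 20% | 72 × 0.20 = 14.4 | 10.8 | 7.2 | 3.6 |
| Ratio | | 1/0.75 = 1.33 | 1/0.50 = 2.0 | 1/0.25 = 4.0 |

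The ratio is simply the reciprocal of the assumed share. It shows the direction of the bias and how sensitive the counts are to it; it does not estimate the bias. The number of activity sessions per woman is not given either, so the number of times each woman is asked cannot be counted.

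**The case against.** The strongest reply has five parts.

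- **The check has a purpose.** It takes place where supervised exercise takes place, and no activity sessions are described for controls. This stands: confining the session check to the intervention arm is not an error in itself.
- **Other routes exist.** A reader might infer that contraindications are collected only from intervention women. The routes in Step 3, and the routine prenatal care that all women receive, rule that reading out. What remains is a difference in intensity, not an absence of collection in controls.
- **No by-arm comparison of this event is planned.** The article says that the DSMB is notified and oversees; it describes no between-arm table or test. The comparative hypothesis, Aim 2b, concerns pregnancy, labor and delivery outcomes abstracted from records, with self-report as backup, and no difference between arms in that process is stated. This stands, and it limits the point to any by-arm summary that the DSMB may see.
- **Asynchronous sessions.** A reader might infer that symptoms are missed there. The article never says that activity sessions are among those that can be asynchronous, so this is an open question and not a demonstrated loss.
- **The full safety protocol is not shown** and may hold common forms. That is possible. But the article does more than leave ascertainment to another document: it states who is asked and when, and this differs by arm.

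**Conclusion.** The point holds in a limited form. For one of the three DSMB events, the repeated active elicitation that the article describes is confined to the intervention arm, and the routes open to both arms are sparser or unspecified. Raw counts of that event would therefore tend to be higher in the intervention arm even with equal true rates.

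This rests on the session checks finding events that the other routes would miss, which is plausible but not quantified in the documents. The ratios of 1.33 to 4.0 depend wholly on the assumed detection share and should not be cited as expected values. The primary outcome and the record-based Aim 2b outcomes are untouched. This is a worthwhile low-cost improvement to safety data, not a flaw in the efficacy comparison.

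**What to change.** Keep the verbal session check as an exercise-safety step. Add one short symptom and contraindication checklist, identical in both arms, to the weekly or monthly REDCap surveys that all women already complete. Base any by-arm DSMB summary on that common source, and list events found only in live sessions separately.

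Safety Considerations and Adaptive Intervention Dosage Changes should also be reconciled: state whether activity sessions can be asynchronous and, if so, how symptoms are captured there.

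The cost is one extra form, under a minute per administration, and more minor events to process. Results reports 12 women enrolled of the planned 144 at the time of writing, so a change made early would cover most of the trial. Events from women followed before the change would need to be marked as collected under the earlier procedure.
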